### Statistical considerations

#### Estimation of sample size

A sample size of 40 participants has been selected in accordance with published guidance for pilot feasibility studies [22, 23]. Further, this was considered to be an achievable number of patients to recruit within the 12 months. Approximately 130 patients undergo oesophago-gastric resections each year for cancer at the Northern Oesophago-Gastric Unit, Royal Victoria Infirmary, Newcastle upon Tyne. It is estimated that 70% will be eligible to take part in the study (i.e. will receive preoperative chemotherapy for adenocarcinoma) [24]. All of these patients will be invited to participate, and it is hoped that enrolment will reach approximately 85–95% as already demonstrated by other prehabilitation studies, which employed home-based interventions [25–27]. In this respect, a sample size of 40 also realistically represents the number of patients that might be expected to be recruited in a year. In a recent study investigating CPET testing after chemotherapy only one participant of 32 recruited participants withdrew consent during the study (3%) [24]: this group of cancer patients is motivated and compliant. It is expected that it will take 12 months to recruit 40 patients to this study.

#### Statistical analysis

Analyses will be conducted using SPSS, version 24.0 (IBM Corp., USA). The primary outcomes will be described using simple descriptive statistics. Characteristics of the patients will be described as the mean (SD) or median (IQR) for continuous data and as the number of patients and percentages for categorical data. Comparison between pre and post intervention data will be analysed using Student’s *t* test or Mann-Whitney’s test for continuous data. The effect of the intervention will be estimated using 75% confidence intervals.

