## Methods

### Study design

This is a prospective, single-group, single-centre pilot study investigating the feasibility and acceptability of a home-based exercise intervention during oncological treatment of patients presenting with operable advanced adenocarcinoma of oesophagus, gastro-oesophageal junction and stomach. Patients will be invited to participate in the study which involves provision of a home-based exercise intervention before, during and after NAC, and in the weeks leading up to surgical resection of the cancer.

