#### Completion of the exercise intervention

The end of the study period is defined as the last full week of exercise before surgery. Participants will complete an end of study CPET, hand grip strength measurement, blood sampling and quality of life questionnaires during the 2 weeks prior to their scheduled surgery. A CT scan, which is performed as part of routine clinical care prior to the surgery, will be used for comparison with the initial CT scan to measure sarcopenia.

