### Study outcomes

The primary and secondary outcomes are defined in Table 1 and Table 2.

**Table 1 Tab1:** The primary outcomes of the study

Primary outcome measures	Definition	Success threshold
Recruitment rate	Proportion of all patients approached who meet the eligibility criteria and agree to enter the study	*50%*
Completion rate	Proportion of all patients that enter the study that remain participants at the end of the defined study period	*75%*
Compliance	Percentage of intervention days when the patient was wearing his/her pedometer, was contactable every week and was recording his/her daily step count	*75%*

**Table 2 Tab2:** The secondary outcomes of the study

Secondary outcome measures	
CPET	Change in VO2 peak (ml/min/kg), change in VO2 at AT (ml/min/kg) and change in FEV1 prior and post intervention
Sarcopenia	Change in amount of L3 level skeletal muscle area determined on CT scan by methodology described by Perthen et al. [21], change in fat composition and volume measured by CT scan and change in grip strength pre and post intervention
Exercise intervention	Change of step count throughout the intervention
Oncological treatment	Number of patients with dose reductions or who terminate chemotherapy early, percentage of planned chemotherapy delivered, admissions to hospital with chemotherapy induced toxicity
Quality of life	Change of score on validated quality of life questionnaires QLQ-C30 and QLQ-OG25 pre and post intervention
Acceptability	Qualitative evidence generated from focus group discussions with participants

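### Mann-Whitney is named for pre/post values in the same patients, and neither the t test nor the 75% interval is said to be paired

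*Protocol article*

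**What the plan says.** Under Study design, the protocol article describes the trial as follows: "This is a prospective, single-group, single-centre pilot study". There is no second group.

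Table 2 (Study outcomes) defines the continuous secondary outcomes as change. For CPET: "Change in VO2 peak (ml/min/kg), change in VO2 at AT (ml/min/kg) and change in FEV1 prior and post intervention". For quality of life: "Change of score on validated quality of life questionnaires QLQ-C30 and QLQ-OG25 pre and post intervention". Muscle area, fat composition and grip strength are also defined as change. Under Completion of the exercise intervention, the routine CT scan before surgery "will be used for comparison with the initial CT scan to measure sarcopenia".

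The Statistical analysis section assigns the tests: "Comparison between pre and post intervention data will be analysed using Student’s *t* test or Mann-Whitney’s test for continuous data". A separate sentence adds: "The effect of the intervention will be estimated using 75% confidence intervals". No paired test is named, and the construction of the interval is not described. The primary outcomes are to be summarised descriptively.

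**The concern.** Each post value has a pre value from the same patient, and the two will normally be correlated. A test for two independent samples ignores that link. It takes the variance of the difference as the sum of two full variances, when the correlated part should be removed.

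Mann-Whitney is such a test; the rank test for pairs is the Wilcoxon signed-rank test. Naming Student's t test beside Mann-Whitney leaves open whether the t test and the interval would also be computed as for independent samples.

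At stake is the secondary aim, a preliminary look at benefit to physiology and quality of life that is meant to inform a larger randomised trial (Study aims). An unpaired analysis would give intervals that are too wide and p-values that are too large. It would also make no use of the variability of within-patient change.

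**Working it through.** **No planned figure to reproduce.** The sample size of 40 rests on pilot-study guidance and achievability. No alpha, power, effect size or SD is given, so no formula yields it, and this point does not depend on it.

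**Inputs from the protocol**
- 40 patients. The 75% completion threshold in Table 1 gives 40 × 0.75 = 30 pairs. The 3% withdrawal quoted from an earlier study (Estimation of sample size) gives 40 × 0.97 = 38.8, about 39 pairs.
- Interval level 75%.

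**Assumptions not in the protocol**
- Equal SDs before and after; pre/post correlation r from 0 to 0.9.
- For the test results, a two-sided 5% level; for power, a true change of 0.4 SD.

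**Standard error, in SD units**
- Independent-sample: √(2/n)
- Paired: √(2(1−r)/n)
- Ratio: 1/√(1−r), whatever n is. At r = 0.5 this is 1/√0.5 = 1.41; at r = 0.9 it is 1/√0.1 = 3.16.

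**Coverage and test level if the pairing is ignored (normal approximation)**
- Coverage of a nominal 75% interval: 2Φ(t(0.875; 2n−2)/√(1−r)) − 1. With n = 30, t = 1.162; at r = 0.5 this is 2Φ(1.643) − 1 = 0.90.
- True level of a nominal 5% test: 2[1 − Φ(t(0.975; 2n−2)/√(1−r))]. With n = 30, t = 2.002; at r = 0.5 this is 2[1 − Φ(2.831)] = 0.0046.

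Results for 30 pairs:

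| r | SE ratio | 75% half-width, unpaired (SD) | 75% half-width, paired (SD) | Coverage of unpaired 75% interval |
|---|---|---|---|---|
| 0 | 1.00 | 0.300 | 0.303 | 75.5% |
| 0.5 | 1.41 | 0.300 | 0.214 | 90% |
| 0.7 | 1.83 | 0.300 | 0.166 | 97% |
| 0.8 | 2.24 | 0.300 | 0.136 | 99% |
| 0.9 | 3.16 | 0.300 | 0.096 | almost 100% |

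With 39 pairs the unpaired half-width is 0.263 SD. The paired half-width is 0.187, 0.145, 0.118 and 0.084 SD at r = 0.5, 0.7, 0.8 and 0.9. The coverage figures are practically the same.

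The true level of the nominal 5% test is about 0.5% at r = 0.5 and 0.03% at r = 0.7.

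**Power by simulation** (3,000 runs, normal data, 30 pairs, change 0.4 SD):

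| r | Two-sample t | Mann-Whitney | Paired t |
|---|---|---|---|
| 0 | 33% | 31% | 31% |
| 0.5 | 27% | 25% | 57% |
| 0.8 | 20% | 20% | 92% |

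The loss is nil at r = 0 and grows with r. For any positive r the error is conservative: it does not create false positives.

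**The case against.** A fair defence has four parts.

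**The t test may be paired.** Student's t test has one-sample, paired and two-sample forms, and outcomes defined as change fit the first two. This stands: the text is ambiguous on the t test, and a two-sample form is suggested but not shown. It does not help Mann-Whitney, which has no paired form.

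**The interval is a separate sentence.** Its construction is not given and could rest on within-patient change whichever test is named. An article may leave that detail to the full protocol or analysis plan. This also stands, so the coverage figures are conditional. A reader might infer that every secondary p-value and interval is wrong, but the text does not support that. The test sentence covers only continuous pre/post data. Treatment delivery ("Number of patients with dose reductions or who terminate chemotherapy early") has no pre/post pair, and acceptability is qualitative ("Qualitative evidence generated from focus group discussions with participants").

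**Large changes would still be seen.** With 30 pairs, the two-sample t test at the 5% level has 67% power (r = 0.5) or 75% (r = 0.8) for a change of 0.6 SD, and 93% or 99% for 0.8 SD. So it cannot be said that a real change would usually be missed. The loss concerns modest changes.

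**Dropout bias is not established.** At the 75% threshold up to 10 of 40 patients could lack a post value, and a reader might infer that they would stay in the pre group and bias the difference. Nothing in the protocol says so, a change outcome needs both values, and the one withdrawal figure quoted is 1 of 32. Restricting the analysis to complete pairs does not remove selection by dropout either.

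**Conclusion.** The point holds in a limited form. Mann-Whitney is stated for paired data and is the wrong test for this single-group design. That is an error in what is written, not a detail left for later. The t test and the 75% interval are not identified as paired and should be.

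The sizes given above apply only if independent-sample forms are actually used. They rest on the assumed r, for which the protocol offers no value, and on equal SDs.

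The error is conservative for positive r. It leaves untouched the feasibility outcomes on which the trial is judged, the sample size of 40, the treatment-delivery outcomes and the focus-group work. It therefore ranks as something that should be fixed, not as a threat to the trial's main purpose.

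**What to change.** Replace the sentence on pre/post comparison, and tie the interval to it, for example:

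> Within-patient changes in continuous outcomes will be analysed with the paired t test, or the Wilcoxon signed-rank test where the differences are clearly non-normal. The 75% confidence interval will be that of the mean (or Hodges-Lehmann median) within-patient change in patients with both measurements.

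Describe separately the baseline values of patients without a post measurement, so that readers can judge how selected the complete pairs are.

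The cost is a short text change in the protocol or analysis plan, made before the analysis. It needs no new data, no more patients and no other software.

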## Introduction

Curative treatment of locally advanced oesophago-gastric adenocarcinoma usually entails neo-adjuvant chemotherapy (NAC) followed by surgery and then postoperative adjuvant chemotherapy. Multimodal therapy has been shown to be superior to surgery alone [1, 2]. This type of major surgery is unfortunately associated with high morbidity and mortality [3, 4]. It has been shown that cardiopulmonary fitness prior to major surgery is related to postoperative outcomes [5]. Previous work has demonstrated a significant and sustained reduction in fitness during NAC given for oesophago-gastric cancer, which not only affects daily activities and quality of life, but also decreases the physical reserve of the patient before they undergo major surgery [6, 7]. Both a reduction in objective cardiopulmonary reserve, measured by cardiopulmonary exercise testing (CPET), and reduction in muscle mass (sarcopenia) on CT scan analysis in the interval between commencing chemotherapy and undergoing surgery has previously been observed [7]. Complications of major surgery are associated with poorer quality of life in the short-term and worse prognosis [8]. Further, they can delay or prevent the administration of post-operative chemotherapy, which may impact on disease recurrence. Preventing these complications may improve surgical outcomes, patient health and survival from oesophago-gastric cancer. In addition, exercise may have beneficial effects on improving immune surveillance and reducing inflammation; reversing abnormalities that may be associated with tumour recurrence and growth [9].

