## Discussion

It is anticipated that during an important teachable moment, the diagnosis and treatment of cancer, our patients will be open to the possibility of improving their fitness during chemotherapy and before major cancer surgery. Having previously demonstrated that fitness declines during oncological treatment we hope an exercise intervention that maintains or improves fitness could lead to better patients’ outcomes in the future. It is possible that the negative impact of NAC on cardiopulmonary fitness could be prevented by implementing a home-based prehabilitation programme during and after NAC, prior to surgery for oesophago-gastric adenocarcinoma. It is hypothesised that exploring a simple and low-cost alternative to high-impact, high-intensity, high-cost regimens could revolutionise the routine clinical care of our patients leaving them better prepared for the stress and morbidities associated with oesophago-gastric cancer surgery. This is a non-randomised, single cohort, unblinded, single-centre feasibility study with a small sample size. This design could lead to potential selection bias however the aim is to take a pragmatic approach which will allow patients to be recruited over a 1-year period and help inform a larger scale randomised control trial.

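### A single-group pre-to-post change is labelled the effect of the intervention, although the protocol itself expects fitness and muscle mass to fall over the same period

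*Protocol article*

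**What the plan says.** All references are to the protocol article.

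- **Analysis.** Under Statistical analysis: "Comparison between pre and post intervention data will be analysed using" a t test or a Mann-Whitney test. The section closes with "The effect of the intervention will be estimated using 75% confidence intervals".
- **Design.** Under Study design: "This is a prospective, single-group, single-centre pilot study investigating the feasibility and acceptability of a home-based exercise intervention". The Discussion confirms it: "This is a non-randomised, single cohort, unblinded, single-centre feasibility study with a small sample size". No control group or external benchmark is described.
- **Expected course without exercise.** The Introduction says: "Previous work has demonstrated a significant and sustained reduction in fitness during NAC given for oesophago-gastric cancer". It adds, for muscle, that a "reduction in muscle mass (sarcopenia) on CT scan analysis in the interval between commencing chemotherapy and undergoing surgery has previously been observed". The Discussion repeats the point for fitness: "Having previously demonstrated that fitness declines during oncological treatment we hope an exercise intervention that maintains or improves fitness" could improve outcomes. None of these places gives a size.
- **Endpoints.** Table 2 lists change in VO2 peak, "change in VO2 at AT (ml/min/kg) and change in FEV1 prior and post intervention", together with changes in L3 muscle area, fat, grip strength and quality-of-life scores.

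**The concern.** The sentence names a causal quantity, but the design delivers only a change over time. That might be a harmless shorthand if the outcomes were expected to stay level without exercise. Here the protocol says the opposite: fitness and muscle mass are expected to fall.

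The mismatch bears on the study's own hypothesis, which is that exercise might prevent the harm that chemotherapy does to fitness. Under the planned label, complete success in that sense would appear as an effect of about zero, and partial success as a negative effect. The secondary results are meant to inform a larger randomised trial in which fitness, sarcopenia and quality of life are outcomes. A mislabelled estimate could make a useful regimen look inert or harmful, or supply that trial with a wrong effect size.

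**Working it through.** **No figure in the plan to reproduce.** The sample size of 40 rests on published pilot-study guidance and achievable recruitment. No effect size, standard deviation, power or significance level is given.

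**Step 1: does the decline lie inside the measurement window?**

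- The first CPET and CT come from routine staging, before chemotherapy (Baseline measurement).
- The intervention starts after one week of monitoring and runs through chemotherapy up to surgery (The exercise intervention).
- The final CPET is done in the two weeks before surgery, and the comparison CT is the routine preoperative scan (Completion of the exercise intervention).
- The Introduction places the earlier falls in CPET measures and muscle between starting chemotherapy and surgery.

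The windows coincide, so the background decline is contained in the pre/post change.

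**Step 2: what the change estimates.** Let D > 0 be the mean decline without exercise and E the true intervention effect. Other time effects are set aside.

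Expected change = E - D, so the bias as an estimate of E is -D.

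If exercise prevents a fraction f of the decline, E = fD and the expected change is (f - 1)D. For any f below 1 the sign is negative, whatever D is.

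**Step 3: illustration for VO2 peak.** The documents give no D. The range 1 to 3 ml/min/kg is an assumption, as are the values of f.

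| Fraction prevented, f | True effect, D = 1 | Change shown | True effect, D = 3 | Change shown |
|---|---|---|---|---|
| 0 | 0 | -1 | 0 | -3 |
| 0.5 | +0.5 | -0.5 | +1.5 | -1.5 |
| 1 | +1 | 0 | +3 | 0 |

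**Step 4: does the confidence level matter?** For a paired mean change, the half-width in SDs of the change is t/√n. With n = 40:

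- 75% interval: 1.168/6.325 = 0.185 SD
- 95% interval: 2.023/6.325 = 0.320 SD

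The table gives the probability that the interval covers the true intervention effect, from the noncentral t distribution. The decline in SDs of the change is assumed. The 30 completers correspond to the 75% completion threshold in Table 1 (0.75 × 40).

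| Assumed decline (SD) | 75% CI, n = 40 | 95% CI, n = 40 | 75% CI, n = 30 |
|---|---|---|---|
| 0 | 75% | 95% | 75% |
| 0.2 | 45% | 77% | 51% |
| 0.3 | 23% | 54% | 32% |
| 0.5 | 2.4% | 13% | 6% |
| 0.8 | 0.01% | 0.15% | 0.07% |

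Both levels lose their nominal coverage as soon as there is a decline. A wider interval softens the loss but leaves the bias unchanged. The fault is in the label, not the level.

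**The case against.** The strongest reply is that this is loose wording in a pilot. The affected outcomes are secondary, and the aim they serve is described as preliminary. The Discussion openly acknowledges the uncontrolled, small, single-cohort design. Effect evaluation is assigned to a later randomised trial, and ChemoFit data are not to be used in it. The authors also say that they hope fitness will be maintained or improved, so a reader is told that no change could be good news.

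Most of this stands, and it limits how serious the point is. It does not remove it. The only design risk the Discussion names is selection bias, which is a different problem from a background trend. The hope of maintained fitness sharpens the conflict: if no change would be a success, an estimate that calls no change a zero effect is mislabelled.

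Some stronger readings are tempting but not supported:

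- **That the 75% level is itself an error, or will generate false signals across Table 2.** A 75% interval is an accepted choice in a pilot. No rule in the protocol turns on whether an interval excludes zero. A count of chance exclusions needs independent outcomes with no true change, which contradicts the expected decline.
- **That the decline is large.** The Introduction calls it significant and sustained and gives no magnitude.
- **That the authors would report harm.** Nothing in the text says how a negative change would be interpreted.

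**Conclusion.** The point holds as a mislabelled estimand. The plan promises the effect of the intervention, but a single group measured before and after can supply only the mean change. By the protocol's own account, that change includes a chemotherapy-related fall in fitness and muscle mass.

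The bias equals the background decline. For fitness and muscle mass its likely direction is against the intervention. Its size cannot be derived from the documents, so the ml/min/kg and coverage figures are illustrations over assumed ranges. What does not depend on those ranges is the sign: full prevention shows a change near zero and partial prevention a negative one. For outcomes such as FEV1, fat and grip strength the protocol states no background trend, so attribution is equally unsupported there but the direction of bias is unknown.

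No corrected effect estimate exists, because one group cannot identify it at any confidence level. The consequence is moderate: it governs what may be concluded from the secondary outcomes and passed to the randomised trial, and leaves the three feasibility outcomes untouched.

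**What to change.** Replace the last sentence of Statistical analysis with:

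> Mean within-patient pre-to-post change will be estimated with confidence intervals and will not be interpreted as the effect of the intervention, because there is no comparison group and fitness is expected to fall during chemotherapy.

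Optionally, if the investigators hold comparable data on earlier patients tested before and after chemotherapy without exercise, the changes in VO2 peak, VO2 at AT and L3 muscle area may be shown beside those data. The display should be descriptive only, with the caveat that regimens, timing and case mix may differ. The protocol refers to earlier work but does not establish that such data are available or comparable, so this step is conditional and brings confounding of its own.

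**Cost.** One sentence, no change to data collection, and a weaker claim on the secondary outcomes.

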#### Qualitative data analysis

Focus group discussions will be audio recorded and transcribed verbatim. Data from each transcript will be analysed by two researchers initially gaining familiarisation with the texts. These will then be coded by the two researchers to identify initial themes. Once all the data has been coded and initial themes identified, there will be further discussion to determine main themes and sub-themes. Following this the original data will be revisited to consider it in relation to the themes produced. These themes will then be named and will help provide a final thematic grip [28].

